## Abstract

**Background:**

During reintegration to daily school life following psychiatric hospitalization, children and adolescents are confronted with various challenges and are at risk for rehospitalization. Tailored post-discharge services could support a successful readjustment and accompany the high-risk transition period after discharge. The study DigiPuR (“Digital gestützte Psychotherapie und Reintegration,” digitally supported psychotherapy and reintegration) aims to establish and to evaluate an innovative digital aftercare program to alleviate challenges during reintegration and improve cross-sectoral care.

**Methods:**

DigiPuR is a randomized controlled trial comparing a digital aftercare service with regular aftercare (TAU) (planned *N* = 150, 25 children/adolescents, 25 parents, and 25 teachers in each group). In the intervention group, direct communication via secure and regular video calls until 8 weeks after discharge and a secure messenger system between the hospital, family, and school, as well as, if needed, external support systems, are established. A longitudinal pre-post-follow-up assessment at admission, discharge, and 8, 24, and 36 weeks after discharge takes place supplemented by a daily smartphone-based ambulatory assessment from a triadic perspective of patients, parents, and teachers. Primary outcomes include whether participants in the intervention group have fewer readmissions and higher treatment satisfaction and health-related quality of life as well as lower symptom severity than participants in the control group.

**Discussion:**

The present study is essential to address the cross-sectoral challenges associated with reintegration into daily (school) life following child and adolescent psychiatric hospitalization and to determine possible needed adaptations in partial or full inpatient settings. If applicability and efficacy of the aftercare service can be demonstrated, integration into regular care will be sought.

**Trial registration:**

ClinicalTrials.govNCT04986228. Registered on August 2, 2021

**Supplementary Information:**

The online version contains supplementary material available at 10.1186/s13063-022-06508-1.

## Background

The prevalence of mental disorders among children and adolescents in Germany and worldwide is between 13 and 18% [1, 2]. For the treatment of mental disorders, in addition to outpatient services, there are partial and full inpatient services as more intensive types of treatment [3]. In 2020, 53,436 patients received full inpatient treatment in child and adolescent psychiatry in Germany [4]. Correspondingly, utilization of the limited inpatient beds in the area of child and adolescent psychiatry is high, with about 89% of available beds in Germany in 2019 being in use [5]. Besides the two areas of general psychiatry and psychosomatics/psychotherapy, this figure is among the highest utilization rates in all departments in German hospitals [5]. Rehospitalization rates have been reported to range from 12 to 57% with percentages tending to be higher for longer follow-up periods [6–12], but most readmissions occurring within the first 3 months after discharge [8–10].

After discharge following psychiatric hospitalization, children and adolescents are confronted with various challenges, emerging predominantly in the academic, social, and emotional domain [13–16]. Academically, children and adolescents need to make up missed school work, with some additionally transferring to a new class or school [14–16]. Socially, children and adolescents report fears of explaining their absence, concerns to lose friendships, and experiences of bullying and stigmatization [14–17]. Emotionally, despite substantial symptom reduction during inpatient treatment, intense negative or overwhelming emotions and residual symptoms often persist or reappear after discharge [14–16, 18, 19]. About 87% of children and adolescents require further assistance after discharge [20]. A seamless transition to outpatient follow-up treatment is desirable, as transfer of therapeutically achieved treatment progress into daily situations usually succeeds only with targeted practice and accompaniment, due to the context dependence of symptomatic behavior [21, 22]. In practice, however, long waiting times, in Germany averaging 5 weeks for an initial consultation and 18 weeks to begin outpatient psychotherapy [23], often prevent a seamless transition between treatment sectors. In case of a child or adolescent starting treatment with a previously unknown outpatient psychotherapist, a sustainable therapeutic relationship, as well as motivation for further treatment, must be newly established, further complicating the transition between inpatient and outpatient care.

Important attachment figures, such as parents or teachers, can help children and adolescents cope with transition-related challenges [24], and it is important to involve them in inpatient psychiatric treatment [25]. Higher parental involvement is associated with a lower risk of the child being rehospitalized [9]. Furthermore, worsening student-teacher relationships as well as increased bullying experiences after hospitalization are associated with higher levels of suicidal ideation in the immediate post-discharge period [26]. However, for many attachment figures, a child’s psychiatric hospitalization is also associated with strain and distress and they often report feelings of incompetence and uncertainties about how to suitably support the child [13, 19, 27, 28]. Supporting attachment figures in the form of providing psychoeducation, strengthening resources, and developing competencies and coping strategies so that they can better understand the child’s situation and adequately deal with it is required and helpful for a successful reintegration [13, 24, 27].

Sufficient and tailored post-discharge support services for patients and their attachment figures could support a successful readjustment and accompany the challenging transition period after discharge [13, 29]. Ideally, case-leading therapists of inpatient treatment seamlessly accompany the reintegration phase for some more weeks after discharge and support readjustment to daily (school) life as well as transfer of treatment successes. The case-leading therapists know the case and all parties involved from the former treatment and can therefore offer support to all parties within the existing therapeutic relationship. This, however, requires sufficient monetary and time resources from all stakeholders.

E-Mental-Health services support people with mental strains through information and communication technologies [30] and offer enormous potential to improve health care [31, 32]. Advantages include a wide reach for treatment services, lack of travel time with more flexible and tailored scheduling for appointments, and low-threshold services [33, 34]. Moreover, the created distance, for example in therapy via videoconferencing, can lead to less dependence on the therapist and to greater disinhibition in statements as well as to additional information by seeing patients in their home environment, which can be helpful for treatment [33]. Demand and use for E-Mental-Health services has once again considerably increased and taken on particular relevance since the beginning of the COVID-19 pandemic [33, 35, 36]. Especially in the context of aftercare, E-Mental-Health services can complement inpatient treatment and close the gap to outpatient treatment by relying on existing therapeutic relationships to seamlessly support the transition from psychiatric hospital to daily life in a low-threshold manner [34, 37]. A recent review on discharge interventions from inpatient child and adolescent mental health care identified only two randomized controlled trials in this area, none of which examined a digitally supported intervention [29]. However, one feasibility study discussed in the review [29] showed a general interest in downloading a smartphone-based application for a digital safety plan at the time of discharge [38]. Studies on the efficacy of digital aftercare services for adults suggest beneficial impacts on patients’ post-discharge development [39–43].

The innovative aftercare program DigiPuR (“Digital gestützte Psychotherapie und Reintegration”, digitally supported psychotherapy and reintegration) aims to stabilize and ideally expand treatment successes after partial or full inpatient child and adolescent psychiatric treatment, therefore reducing a worsening of symptoms and rehospitalizations. In the intervention group, direct communication via secure and regular video calls and a messenger system between the hospital, family, and school, as well as, if needed, external support systems, are established. Thereby, problems can be identified and addressed early from multiple perspectives and transitions into outpatient structures can be arranged where necessary. Taking the social environment of children and adolescents into consideration when examining emotional and behavioral problems is consistent with the principle of multisystemic therapy [44]. Efficacy of this digital aftercare in the intervention group is compared to an active control group with regular aftercare within a randomized controlled trial using a naturalistic parallel group study design. A longitudinal pre-post-follow-up assessment at admission, discharge, and 8, 24, and 36 weeks after discharge supplemented by a daily smartphone-based ambulatory assessment from a triadic perspective of patients, parents, and teachers allows for a close investigation of between-person differences and within-person processes in patients’ daily lives. The supplemented ambulatory assessment moreover allows ecologically valid measurements in participants’ daily lives, at the same time reducing retrospective bias [45]. Answers from the ambulatory assessment are graphically processed for the therapists on a weekly basis during aftercare [37]. The assessments are based on the comprehensive conceptual model of outcomes of mental health care for children and adolescents [46]. Accordingly, treatment success and service effectiveness are not only considered as symptom reduction on the individual level, but also related to interactions with the environment in different settings (e.g., home, school, community) [46]. The model proposes five outcome domains (symptoms, functioning, consumer perspectives, environments, systems) in which impact of interventions can be seen [46]. To address these domains, the assessments in DigiPuR include a multi-perspective view on the reintegration phase and instruments used for assessment reflect the domains. The comprehensive assessment serves to examine the general applicability and acceptance as well as the efficacy of this new digital aftercare program for the development of structures specifically for aftercare. Implementing DigiPuR in clinical practice thereby requires a balancing of scientific comparability and practical feasibility in the conception of the design as well as in the scientific evaluation, focusing on aftercare which is flexible and tailored to the needs of the individual patients.

### Hypotheses

DigiPuR examines whether the reintegration of children and adolescents after their stay in a psychiatric hospital can be facilitated by digitally supported, cross-contextual aftercare. Four hypotheses emerge for the primary outcomes. First, we hypothesize readmission rates to be lower at the post- and follow-up time points in the intervention group than in the control group (treatment-as-usual; TAU). Second, we hypothesize satisfaction with treatment to be higher at the post-time point in the intervention group than in the control group. Third, we hypothesize health-related quality of life to develop better over time (pre-post follow-up) in the intervention group than in the control group. We do not necessarily expect the intervention group to improve in absolute values over time, as measures can decline after discharge, indicated by high rates of readmissions [8, 10]. Rather, we expect the intervention group to develop better over time than the control group, meaning that even a stabilization of values might be considered a success. Fourth, we hypothesize symptom severity to develop better over time (pre-post follow-up) in the intervention group than in the control group. In line with the last two hypotheses, a better development in the intervention group than in the control group is also expected for the secondary outcomes on stress, self-efficacy, and perceived competence, including ambulatory assessment on well-being, affect, sleep quality, school situation, and social relationships.

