#### Pre-post-follow-up assessment

Admission and discharge assessment as part of the standard hospital assessment are carried out on paper questionnaires (in exceptions where necessary online) through trained staff during the partial or full inpatient hospital stay in the period from preliminary talk to admission until 1 week after admission and in the period from 1 week before discharge until discharge (pre). For the post, follow-up 1, and follow-up 2 assessment (8, 24, and 36 weeks after discharge), the participants receive an e-mail containing a link for an online survey on the SoSci Survey platform [50], which they can respond to at home via the browser of their computer, tablet, or smartphone within 1 week. At each time point of assessment, the survey lasts no longer than about 45 min.

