#### Instruments

The instruments used in DigiPuR (see Table 1) are chosen to cover the five domains (symptoms, functioning, consumer perspectives, environments, systems) of the comprehensive conceptual model of outcomes of mental health care for children and adolescents [46]. The instruments and scales used in the pre-post-follow-up assessment and the ambulatory assessment are briefly described in the following, sorted according to the five domains. Item formulations were adapted where necessary so that they are understandable and suitable for both children and adolescents. Items are only presented if their content is relevant to the respective group (e.g. items on satisfaction with the program for video calls only when it was used). Primary outcomes are number of readmissions, satisfaction with treatment, health-related quality of life, and symptom severity; all others are secondary outcomes (see Table 1). As there is a great heterogeneity of diagnoses in the patient sample, the evaluation aims to assess the reintegration phase and the well-being of patients globally and across disorders. General constructs relevant to different disorders were selected and instruments were used for comparability across the age range.

**Table 1 Tab1:** Overview of assessed outcomes, assigned domains, instruments, and raters at the different study time points

Outcome	Domain [46]	Instrument or scale	Rater	Study period				
				Enrollment	Allocation	Post-allocation		
				Admission	Ambulatory assessment (2 weeks before discharge until 8 weeks after)	Pre (discharge)	Post (8 weeks after discharge)	Follow-up (24 and 36 weeks after discharge)
Symptom severity	Symptoms	DISYPS-III SCREEN [52]	CA, P*, T*	x		x	x	x
Stress vulnerability and coping strategies	Symptoms (part 1), functioning (part 2)	Adapted from SSKJ-3-8R (parts 1 and 2) [53]	CA	x		x	x	x
Self-efficacy	Functioning	WIRKSCHUL [54], WIRKSOZ [54], WIRKLEHR [54], WIRKELTERN (self-development)	CA, P, T	x		x	x	x
Health-related quality of life	Consumer perspectives, environment	KIDSCREEN-27 [55]	CA, P*	x		x	x	x
Occupational well-being	Environment	Emotional exhaustion [56], enthusiasm for teaching [56]	T			x	x	x
Satisfaction with treatment	Consumer perspectives	Adapted from FBB [57]	CA, P, T, TH				x	
Satisfaction with technical components	Consumer perspectives	SUS [58], self-development	CA, P, T, TH				x	
Expectation of change	Consumer perspectives	Adapted from patient’s expectation of change [59]	CA, P			x		

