Parental stress	Consumer perspectives, environment	EBI [60]	P	x		x	x	x
Parental strain	Consumer perspectives, environment	BSCL [61]	P	x				
Competence self-concept in dealing with students	Environment	Competence self-concept in dealing with students [62]	T			x	x	x
Professional competence in dealing with students with mental disorders	Environment	Self-development, Selection of different items from [54, 56, 63–66]	T			x	x	x
Number readmissions, and general information	All domains	Hospital documentation, self-development	P, T, TH	x		x	x	x
General well-being	Symptoms	Self-development	CA, P, T, P*, T*		x			
Affect	Symptoms	Affect [67]	CA, P		x			
Sleep quality	Symptoms	Sleep quality [67]	CA		x			
School absenteeism	Functioning	Self-development	CA		x			
School day	Functioning	Academic success [68]; adapted from KIDSCREEN-27 [55]	CA, T*		x			
Relationship with peers, parents and teachers	Consumer perspectives, environment	Peer relatedness [69], adapted from KIDSCREEN-27 [55]	CA, P*, T*		x			
Support from the hospital	Systems	Self-development	T		x			

*Note*. All items presented in German. *CA* children and adolescents, *P* parent, *T* teacher, *TH* therapist. *Assessed regarding the child or adolescent

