##### Hospital documentation on general information

General and professional information about participants is obtained from hospital documentation and anamnesis forms for families (e.g., diagnoses, medications, level of psychosocial functioning, duration of treatment) and is collected from teachers at study inclusion (e.g., years in the profession, type of school, teaching load, professional contact with students with mental disorders). Further information for a health economic evaluation is obtained by analyzing controlling data (e.g., percentage of readmissions; travel times; contact via messenger) and the therapist’s documentation (e.g., worksheets on weekly goals; missed appointments; cooperation with support systems; implementation of therapy suggestions).

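### Hypothesis 1 does not fix which readmission measure or time point decides it, and the general group-by-time rule does not test the lower level that it states

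*Protocol article*

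**What the plan says.** The protocol article describes the readmission outcome in several ways.

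- **Hypotheses**, hypothesis 1: "we hypothesize readmission rates to be lower at the post- and follow-up time points in the intervention group than in the control group". The section on the pre-post-follow-up assessment puts post at 8 weeks and the two follow-ups at 24 and 36 weeks after discharge.
- **Instruments**, outcome list: "Primary outcomes are number of readmissions, satisfaction with treatment, health-related quality of life, and symptom severity".
- **Table 1**: the row is labelled "Number readmissions, and general information" and is marked at admission, discharge, post and follow-up.
- **Abstract, Methods**: "participants in the intervention group have fewer readmissions", with no time point.
- **Hospital documentation on general information**: "percentage of readmissions", listed among the health-economic data.

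The Statistical analyses section does not mention readmissions by name. Its general rule assigns a mixed ANOVA to every outcome measured pre-post-follow-up and takes a significant interaction of group and time point as evidence of success.

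**The concern.** The share of patients readmitted at least once and the number of readmissions per patient are different outcomes, and they can rank the two arms differently. Three time points add a second open choice. Hypothesis 1 does not say whether one favourable time point is enough, whether all must agree, or whether one is decisive. By contrast, hypothesis 2 (satisfaction) names a single time point.

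The timing matters here. The intervention runs to 8 weeks, and the Background reports "most readmissions occurring within the first 3 months after discharge". An early difference that fades by 36 weeks is a plausible result, and the article does not say how it would be read. A measure or time point chosen after the data are seen could decide whether a primary hypothesis counts as supported.

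**Working it through.** **Inputs from the article.** 25 children or adolescents per group; assessments at 8, 24 and 36 weeks; reported readmission rates of 12 to 57% (Background). The sample size section gives no alpha, power or effect size, so there is no planned figure to reproduce.

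**Assumptions.** Two-sided 5% per test, cumulative windows from discharge, and the readmission rates stated below.

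**1. The measure can change the answer (constructed data).** Intervention: 3 of 25 patients readmitted, 4, 3 and 3 times. Control: 10 of 25 readmitted once each.
- Shares: 12% vs 40%. Pooled share 13/50 = 0.26; SE = √(0.26 × 0.74 × 2/25) = 0.124; z = 0.28/0.124 = 2.26; chi-square p = 0.024 (Fisher p = 0.051).
- Counts: 10 vs 10, rate ratio 1.00, p = 1.0. If each of the three intervention patients had 4 readmissions, the counts would be 12 vs 10, rate ratio 1.20, in the opposite direction.

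**2. The time point can change the answer (constructed data, cumulative patients readmitted).**

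| Week | Intervention | Control | Chi-square p | Fisher p |
|---|---|---|---|---|
| 8 | 1/25 | 7/25 | 0.021 | 0.049 |
| 24 | 6/25 | 9/25 | 0.35 | 0.54 |
| 36 | 10/25 | 10/25 | 1.0 | 1.0 |

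**3. The general rule does not match the hypothesis.** Let d be the group difference in readmission at a time point. Hypothesis 1 concerns d itself. The interaction concerns changes in d. If d is the same at 8, 24 and 36 weeks, every interaction contrast over those points is d − d = 0, although hypothesis 1 is true at all three. In the table above d is −0.24, −0.12 and 0. That is an interaction pattern, yet the advantage is disappearing. If discharge entered the model with zero readmissions in both arms, a constant later difference would produce an interaction, but the article does not say which time points enter for this outcome.

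**4. Chance of a false claim if any time point suffices.** For three independent tests the figure would be 1 − 0.95³ = 0.143. The cumulative windows overlap, so simulation is needed: 25 per arm, the same Poisson or gamma-Poisson readmission process in both arms, 8,000 to 40,000 trials per scenario.

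| Criterion | Chance of at least one p < 0.05 under no effect |
|---|---|
| One pre-specified measure and time (chi-square or t test) | 0.045–0.061 |
| Share, any of three times, chi-square | 0.08–0.13 |
| Count, any of three times, t test | 0.07–0.10 |
| Share, any of three times, Fisher | 0.02–0.06 |
| Share (chi-square) or count (t test), any of three times | 0.12–0.16 |

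The three any-of-three rows cover assumed 36-week rates of 12 to 57%. The first and last rows cover 30 to 57%.

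**5. Chance of success under an assumed effect** (20/35/40% in control vs 7/15/20% in intervention at 8/24/36 weeks). Fisher: about 0.35 if any time point suffices, 0.23 at 36 weeks alone, 0.08 if all three are required. Chi-square, all three required: 0.17.

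**The case against.** **The article already gives a rule.** Read literally, the mixed ANOVA covers every outcome measured pre-post-follow-up, and Table 1 marks readmissions at those times. It would therefore be wrong to say that no analysis rule could apply. But the rule leaves rate versus number open and, by step 3, tests something other than hypothesis 1. It adds another candidate criterion and does not settle the choice.

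**Rate and number need not conflict.** The Background uses rates to mean percentages, and the number in Table 1 could be the recorded variable from which a percentage is formed. That reading is possible, but the outcome list makes the number itself primary.

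**The word joining post and follow-up may mean all time points.** If so, there is no inflation. That is a fair reading, but no rule states it.

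**This is detail for the analysis plan.** The exact test is. Which readmission measure is primary, and when, is worded inconsistently in this document, and that can be judged here.

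**Stronger readings that the article does not support.** A reader might infer that the false-positive rate is simply doubled. That is roughly so with chi-square and nearly so with counts, but not with Fisher, and the article names none of these tests for readmissions. A reader might also infer that requiring all three time points makes success almost impossible; under the assumed effect it is 0.08 to 0.17, and much of that is sample size. A non-significant result would fail to support hypothesis 1, not refute it. Finally, cumulative windows are an inference; the article does not say.

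**Conclusion.** The point holds. A primary outcome is worded in two ways, has three time points with none named as decisive, and falls under a general success rule that does not test the stated hypothesis. The same trial could be reported as supporting or failing to support hypothesis 1. This conclusion rests on the wording and on steps 1 to 3, and does not depend on the simulations.

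The size of any error inflation depends on the test: about 0.08 to 0.13 with chi-square and 0.02 to 0.06 with Fisher if any of the three time points may carry the claim. These figures assume cumulative windows, 25 per arm, two-sided 5% per test and the stated rates. The matter should be corrected, and it is inexpensive to correct.

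**What to change.** Before outcomes are seen:

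- Use one readmission measure in the hypothesis, the outcome list and Table 1.
- Name one deciding window and one matching between-group comparison in all randomised patients. One workable choice is the share with at least one psychiatric readmission from discharge to 36 weeks, because it uses the full follow-up. Another window could be defended, given the 8-week intervention and the early clustering of readmissions.
- State that this comparison, not the group-by-time interaction, decides hypothesis 1, and that the other time points and the count are supportive.
- State whether the short emergency inpatient stays described under Participants and recruitment count as readmissions, and how readmissions are recorded once a longer stay has ended participation.

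The cost is a few sentences and no new data. The downside is that a difference seen only at another time point could not be claimed as the primary readmission result.

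The change does not cure low power. By the usual normal approximation for two proportions, 25 per group has 11%, 24% and 53% power to detect a halving from control rates of 12%, 30% and 57%; 80% power would need 356, 121 and 47 per group.
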